### Outcomes

All outcomes will be measured using blinded assessment processes at the two study endpoints of six and twelve months post-discharge. Each outcome will be a comparison between the control and intervention groups. A proposed conceptual framework for the standardized evaluation of chronic disease management interventions has been considered in the selection of the trial outcomes and further trial evaluation [28]. Using a framework to guide outcome selection has not only helped to ensure that we are measuring the important clinical outcomes from the intervention, but also highlighted the individual steps of the intervention that require monitoring. Monitoring these individual steps, such as pharmacist detection of drug-related problems and GP acceptance of pharmacist recommendations, is important to measure the level of alignment between the theoretical plan and the practical application of the intervention. Such detailed monitoring and outcome reporting may also elucidate areas of practice worthy of further focus in future research.

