### Primary outcome

The primary outcome will be the proportion of patients who are adherent to a complete, guideline-based ACS medication regimen at the trial endpoints. The accepted definition of adherence for this trial will be a medication possession ratio (MPR) of 80% to 120% for all guideline-based medications, which is a commonly accepted cut-off for this measure [35-39]. MPR will be determined by dividing the total number of days of medication supplied by the total specified time period. This value can be multiplied by 100 in order to be reported as a percentage of the time that the patient had medication available to take, a commonly used surrogate measure of adherence. During the baseline interview, we intend to record all possible pharmacies that a patient may attend in order to make the dispensing records complete. If, however, there is a significant shortfall in the completeness of dispensing records, we will use self-report of medication adherence as an alternate measure. The four-item Morisky adherence questionnaire will be used for this purpose [40]. This is a well-validated instrument, being used previously with good predictive validity in patients at risk of cardiovascular disease [40,41]. In the case where a patient has a clearly documented contraindication to one of the four guideline-based medication classes, their medication regimen may still be considered 'complete' provided they are taking all other guideline-based medications. For example, a patient with asthma not taking a beta-blocker but still taking aspirin, an ACE inhibitor, and a statin, will be considered in the same group as those prescribed all four medications. This primary outcome comprehensively assesses the overall impact of the intervention on both GP prescribing behaviors and patient medication-taking behaviors. In order to separately measure the recognized problem of persistence with guideline-based medications, we will complete a secondary analysis of the primary outcome in the group of patients who are prescribed a complete, guideline-based medication regimen at the time of discharge from hospital.

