In addition to these questionnaires it is important to note that for the purpose of testing for predictors of adherence, we will be considering two separate models. In the first model, adherence will be measured by the MPR and in the second model, adherence will be measured by the Morisky Adherence Questionnaire [40]. Both measures have individual benefits and limitations to their use, but have been extensively validated in cardiac settings [35,40,41,62,63]. It was considered important to include the second model using a questionnaire to assess adherence in order to maintain consistency with the reliance on questionnaires as the method of assessment for all concepts. The complete questionnaire set chosen for this study can be viewed in Additional file 1.

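### The primary adherence measure may change from dispensing records to patient self-report on an undefined trigger, and the substitute as described does not show a complete regimen

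*Protocol article*

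**What the plan says.** All of the following is in the protocol article.

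- **Outcome** (Primary outcome): "The primary outcome will be the proportion of patients who are adherent to a complete, guideline-based ACS medication regimen at the trial endpoints".
- **Measure** (same section): "The accepted definition of adherence for this trial will be a medication possession ratio (MPR) of 80% to 120% for all guideline-based medications".
- **Purpose** (same section): the outcome is said to be one that "comprehensively assesses the overall impact of the intervention on both GP prescribing behaviors and patient medication-taking behaviors".
- **Fallback** (same section): "If, however, there is a significant shortfall in the completeness of dispensing records, we will use self-report of medication adherence as an alternate measure". The instrument is named: "The four-item Morisky adherence questionnaire will be used for this purpose". The section gives no completeness threshold, no cut-off score, and no statement of whether the switch is made per patient or for the whole trial.
- **Both measures are planned in any case** (Process outcomes, on predictors of adherence): "In the first model, adherence will be measured by the MPR and in the second model, adherence will be measured by the Morisky Adherence Questionnaire".
- **Timing** (Data collection): requests for dispensing records and the questionnaire mail-out belong to the same follow-up points, six and twelve months.
- **Blinding** (Outcomes): "All outcomes will be measured using blinded assessment processes at the two study endpoints".

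**The concern.** A primary endpoint should be fixed before the data that could influence its choice exist. Here one clause lets the measure behind the headline result depend on how complete the follow-up data turn out to be, with no stated limit on that judgement.

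The substitute is also not a second reading of the same quantity. MPR across all classes fails a patient who was never prescribed a class, or whose doctor stopped it. A general self-report of medicine-taking, scored without reference to the classes, can pass that patient. The trial would then report an outcome that no longer carries the prescribing component the protocol claims for it.

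Finally, dispensing records do not depend on what the patient chooses to say, whereas a questionnaire does. In this trial one arm has had a home visit from a pharmacist trained in improving adherence.

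**Working it through.** **1. The plan's own sample size.** Inputs from Sample size: 45% in controls, a 15-point difference (so 60%), 80% power, alpha 0.05 (taken as two-sided).

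Uncorrected n = [1.960·√(2·0.525·0.475) + 0.842·√(0.45·0.55 + 0.60·0.40)]² / 0.15² = 172.8, so 173 per group.

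With continuity correction: (172.8/4)·[1 + √(1 + 4/(172.8·0.15))]² = 185.9, so 186 per group. The total is 372/0.80 = 465. Both stated figures reproduce and are not in question. They are stated for the regimen-based outcome; the article gives no expected rate for the questionnaire.

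**2. What can be known when the switch is decided.** Record completeness is visible only after pharmacies have been asked for records at six and twelve months. The questionnaire goes out at the same points. Both adherence results can therefore be in hand when someone decides whether the shortfall is large enough.

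**3. Construct, side by side.**

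| | MPR as defined | Questionnaire as described |
|---|---|---|
| Refers to each drug class | Yes, all guideline-based medications | Not stated |
| Detects a class not prescribed or stopped by the GP | Yes | Not by itself |
| Source | Pharmacy records | The patient |
| Cut-off for adherent | 80% to 120% | Not stated |

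**4. One-sided over-reporting, no true effect.** Assumed: the switch applies to the whole trial, n = 186 per arm, the control self-report rate is 45%, and the intervention arm over-reports by b. With m the mean of the two rates, SE₀ = √(2m(1−m)/186), and SE₁ is the unpooled equivalent. The rejection probability is Φ((b − 1.96·SE₀)/SE₁) plus the lower tail.

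- b = 0.05: SE₀ = 0.0518, SE₁ = 0.0517; Φ(−0.996) = 0.160, lower tail 0.002, total **16%**.
- b = 0.075: Φ(−0.514) = **30%**.
- b = 0.10: Φ(−0.031) = **49%**.

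If the control self-report rate were 70%, the figures for 5 and 10 points would be 19% and 61%.

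**5. Equal misclassification in both arms, true rates 45% and 60%.** The observed rate is p·sens + (1−p)·(1−spec), with sensitivity and specificity assumed.

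- 0.9/0.7: 57.0% v 66.0%, difference 9.0 points, power 43%.
- 0.8/0.5: 63.5% v 68.0%, difference 4.5 points, power 15%.

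Without misclassification, the same uncorrected test at 186 per arm has 83% power.

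**6. Upper bound on a results-driven choice, no reporting bias.** If either of two null test statistics could be taken as primary, two-sided type I error would be 9.8% at correlation 0 (1 − 0.95² = 9.75%), 9.0% at 0.5 and 8.3% at 0.7 (simulation, 2,000,000 draws), instead of 5%.

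**The case against.** **The threshold may sit elsewhere.** An article can leave the definition of a shortfall, and who decides, to the full protocol or the SAP. That stands, so the missing threshold alone would not be a finding. No later document undoes what the article itself fixes, however: a named, patient-reported substitute for the primary measure.

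**A reader might infer that the endpoint can be chosen on the results.** The text does not support that. It ties the switch to record completeness, which can be judged without comparing arms. The instrument is named in advance, and the baseline interview is to list every pharmacy a patient may use. What remains is that nothing stated prevents the results from being seen first.

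**A reader might infer that the fallback abandons the complete-regimen criterion.** It may replace only the adherence element, leaving completeness to be established some other way. The questionnaire itself is in an additional file that is not shown. The supportable criticism is narrower: as described, the substitute has no link to the four classes, and no other route to completeness is given.

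**A reader might infer a flat contradiction on blinding.** Blinded assessment processes can mean blinded collection and scoring. That reading is fair, but it cannot extend to a respondent who knows whether the pharmacist came. The same limit applies to the quality-of-life and smoking self-reports.

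**A reader might infer that the switch would favour the intervention.** That is possible but not shown. Steps 4 and 5 of the working point in opposite directions, and both rest on assumed reporting errors.

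**Imputation has limits.** Supply from an unlisted pharmacy appears as a falsely low MPR, not as a missing value, so imputation alone would not repair it. This stands and shapes the fix.

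**Conclusion.** The concern holds in this form: the article permits a data-dependent change of the primary adherence measure, on an undefined trigger, to a self-report that does not by itself show that a complete regimen is prescribed and taken. The blanket blinding statement cannot cover the people answering that self-report.

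The size is conditional. If the switch were made for the whole trial and only the intervention arm over-reported by 5 to 10 points, two-sided rejection with no true effect would be about 16%–49% instead of 5% (control rate 45%). If misclassification were equal in both arms, the 15-point difference would shrink to 9.0–4.5 points and power would fall to 43%–15% under the assumed sensitivities and specificities. None of these error sizes comes from the documents, so they are not estimates of this trial's error rate. The sample size calculation is correct for the outcome it addresses. The clause is a contingency that may never be used, but it governs the primary result and is cheap to remove.

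**What to change.** 1. Keep MPR as the only primary adherence measure and delete the switch.
2. Define record completeness per patient, for example records obtained from all pharmacies the patient listed, and have it judged blind to arm.
3. Treat patients with incomplete records as missing. Use multiple imputation within arm, plus a delta-shift sensitivity analysis. Let that analysis also cover supply from unlisted pharmacies, by allowing some patients with apparently complete records but low MPR to be adherent, at rates that may differ by arm.
4. Report the self-report questionnaire only as a secondary or sensitivity measure.
5. Limit the blinding statement in Outcomes to record- and registry-based outcomes and to blinded data handling.

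**Cost.** This needs a wording change and modest analysis work. The sample size stays at 186 per group and 465 in total, and no new data are needed because both measures are already planned. The Trial status section says recruitment has not begun, so the change can precede any data.

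**Downside.** If records are very incomplete, the primary estimate will be less precise and will depend on the imputation assumptions, and the report must say so. The deleted fallback would not have escaped missing data either, since it relies on mailed questionnaires being returned.

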### Secondary outcomes

Secondary outcomes will include hospital readmission rates, length of hospital stays, changes in quality of life, cardiac rehabilitation completion rates, smoking cessations rates, and mortality. Hospital readmissions and mortality will be further categorized as ACS-related or due to other causes. Quality of life will be measured at six weeks post-discharge as a baseline, pre-dHMR measure and again at both study endpoints. The Euroqol 'EQ-5D 3 L' [42] will be used to measure general quality of life and the Seattle Angina Questionnaire (SAQ) [43] will be used to measure cardiac-specific quality of life. Both instruments have been validated when administered individually [43-46] and in combination [47] to assess quality of life in patients with coronary heart disease. In addition to a self-report of smoking status at baseline and the study endpoints, we will be further categorizing each smoker's dependence on cigarette smoking using the Fagerstrom Test for Nicotine Dependence (FTND) [48].

### Process outcomes

In addition to reporting the important clinical outcomes that may be affected by the intervention, it is also recognized that there are many individual components of such interventions that can be measured and may highlight barriers or enablers to the overall success of the intervention [28]. From the professional side of the dHMR, it will be important to measure GP acceptance of the intervention through approval of dHMR referrals, pharmacists' recognition of drug-related problems, the clinical relevance of the drug-related problems identified, and GP acceptance of pharmacists' recommendations. Figures 4 and 5 represent our plans to measure the effect of these professional and organizational barriers on trial implementation.

**Figure 4 F4:**
[figure not shown]
**Evaluation of the professional-focused components of the intervention **[28]. The blue text in this figure highlights where the professional focused components of the intervention fit into the Lemmens *et al. *framework. dHMR: Directed Home Medicines Review.

**Figure 5 F5:**
[figure not shown]
**Evaluation of the health system's impact on the implementation of the intervention **[28]. The blue text in this figure highlights how the local health-system structure may affect the implementation of the intervention described within this trial protocol. Again, the relevant points raised by the Lemmens *et al. *framework have been considered. dHMR: Directed Home Medicines Review.

From the patient's perspective it is important to consider, firstly, how the dHMR process may influence psychological variables that have been previously recognized as relevant to adherence behavior, as well as how strongly these variables correlate to the outcome of adherence within this particular trial setting. The concepts we have chosen to consider and the validated instruments that will be used to evaluate each construct are detailed in Figure 6.

**Figure 6 F6:**
[figure not shown]
**Evaluation of the patient focused component of the intervention **[28,40,49-54]. This figure highlights the comprehensive evaluation that we have designed for the patient-focused component of the intervention. IPQ: Illness Perception Questionnaire; PHRQ: Perceived Health Risk Questionnaire; BMQ: Beliefs About Medicines Questionnaire; TABS: Tool for Adherence Behavior Screening; MPR: Medication Possession Ratio.

The concepts of knowledge [55-57], illness perception [49,58], beliefs about medications [59,60], and self-efficacy [50,61] have all been studied separately in coronary heart disease populations. In developing the conceptual framework for the evaluation of chronic disease interventions, however, Lemmens *et al. *recognized the important interrelations between these concepts and how this can affect the ultimate outcome of patient behavior change [28]. Risk perception [51] and adherence-specific behaviors [52] are two lesser studied concepts that may also affect or predict adherence and, as such, have been added to our model of assessment. As discussed, we consider it important to measure and report on the effect of the dHMR on these individual concepts, as well as the validity of the individual concepts as predictors for adherence within this trial setting. Again, the latter has been investigated on an individual basis for some concepts, but the different trial setting and the inclusion of further variables may result in alternate outcomes. The full details of the predictors of adherence recognized in our ACS population will be published elsewhere. The following is a brief summary of the questionnaires selected for this purpose: to assess medication knowledge we have selected recall of individual medication purpose as adapted from Hope *et al. *[53]; for illness perception we have selected the eight quantitative items of the Brief Illness Perception Questionnaire (Brief IPQ) [49]; for risk perception we have selected the Perceived Heart Risk Questionnaire (PHRQ) [51]; for beliefs about medications we have selected eight items from the Beliefs About Medicines Questionnaire (BMQ) [54] and developed two items to assess the impact of cost 'The cost of my medications makes it difficult for me to take them regularly' and 'Medications are not good value for money' which will be assessed on the same 5-point Likert scale as the BMQ questions; for self-efficacy we have selected seven items from the Cardiac Self-Efficacy Scale [50]; for adherence-specific behaviors we have selected the Tool for Adherence Behavior Screening (TABS) [52].

Further detail on the reasoning behind each questionnaire's selection and the reasons for abbreviation of full questionnaires, where relevant, will be discussed in a future publication on the predictors of adherence. All of these questionnaires have been validated in populations of patients with coronary heart disease.

In addition to these questionnaires it is important to note that for the purpose of testing for predictors of adherence, we will be considering two separate models. In the first model, adherence will be measured by the MPR and in the second model, adherence will be measured by the Morisky Adherence Questionnaire [40]. Both measures have individual benefits and limitations to their use, but have been extensively validated in cardiac settings [35,40,41,62,63]. It was considered important to include the second model using a questionnaire to assess adherence in order to maintain consistency with the reliance on questionnaires as the method of assessment for all concepts. The complete questionnaire set chosen for this study can be viewed in Additional file 1.

### Sample size

We are aiming to detect a change in the primary outcome of 15% between the control and intervention groups. This predicted change is based on the results of the DMACS study, whereby a 12% post-intervention improvement was observed on the proportion of patients taking the same four guideline-based medications at discharge [3]. To detect a change of 15%, assuming a control group result of 45%, a power to detect a difference of 80% with alpha = 0.05, we require a minimum sample size of 186 patients per group. To account for an approximate dropout rate of 20%, we aim to enroll 465 patients in total.

### Data collection

Baseline data collection will occur in hospital at the time of enrolment, immediately post-discharge from hospital and at six weeks post-discharge - when the participants will be sent their first questionnaire set. The in-hospital baseline data collection will include the recording of traditional coronary risk factors, as well as the 'cholesterol' version of the INTERHEART Modifiable Risk Score (IHMRS) [64]. This will allow for baseline comparison of risk between the two groups. Although not validated to calculate risk in a population of patients following a coronary event, the IHMRS requires the recording of risk factors in a way which emphasizes their correlation to their level of actual risk and this remains relevant, regardless of the patient's degree of heart disease. For example, the IHMRS requires the recording of smoking status into several cutoffs depending on the number of cigarettes smoked per day, which correlates independently to heart attack risk, as opposed to simply recording cigarette smoking status in an arbitrary fashion, which is of lesser value with regard to risk comparisons. The final baseline data collection point of six weeks post-discharge for questionnaire mail-out reflects our intention to gauge each patient's status on each of the questionnaires in the time directly before the HMR and not while in hospital, as factors, such as adherence behavior, may be very high in hospital but may significantly decline over time following discharge [2,3,14,65,66]. Patients in the intervention group will be asked to ensure that they complete their questionnaire before their pharmacist visit and pharmacists will record whether or not this has happened as reported by the patient. Patients in the control group will be given a reminder telephone call if their questionnaires have not been returned by three weeks from the mail-out date.

Accredited pharmacists' successful completion of the education and assessment package will be required prior to starting any trial dHMR. This will be recorded through an online system, specifically designed to guide each pharmacist through to completion of this package, while also monitoring their usage levels of the education website via separate log in codes. Although completion of the package is encouraged by an AUD$50 honorarium, program completion cannot be enforced beyond this level and those patients receiving a dHMR by a pharmacist who has not successfully finished the education and assessment package prior to the dHMR interview will be excluded from the secondary on-treatment analysis, as discussed in the 'statistical analysis' section.

Following the dHMR interview, data collection starts with the pharmacist's dHMR report and the agreed, patient-GP management plan. Collection of these documents will allow for assessment of pharmacists' recognition of drug-related problems, the recommendations made to improve these problems, and the GPs' acceptance of these recommendations, as described in Figures 4 and 5. Telephone follow-up will be considered two months after the interview if these reports and management plans have not been received. Recent amendments to the Medicare-funded HMR reimbursement process have strongly increased the requirement that an agreed management plan be formulated following all HMRs, which should help facilitate this data collection point.

Six and twelve months post-discharge follow-up will include requests to community pharmacies for patient dispensing records, hospital register checks for readmissions and length of stays, a death's registry check for mortality, and questionnaire mail-out with a three-week phone call reminder.

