### Intervention

Patients in the intervention group will receive a dHMR at approximately two months following discharge as well as usual care. The time of two months post-discharge was selected as previous studies of ACS patients have demonstrated that the period between one and three months post discharge is when patients are most vulnerable for medication discontinuation [2,3,32]. This suggests that a service addressing both the educational and clinical management aspects of therapy may be most beneficial when offered in this time period.

Based on the existing funding arrangements and recommended reasons for referral, the HMR service is currently available in Australia for all ACS patients following hospital discharge [16]. The uptake of this service, however, may be largely limited by the absence of HMR referral systems in this transitional period. Furthermore, the currently available service could be tailored to maximize the potential for benefit from this service in the ACS population. We propose to add to the existing HMR service in several ways, making the proposed dHMR service more directed toward the ACS population.

Typically, HMRs are ordered by a referral letter generated by the patient's GP. Referral letters may vary significantly in their level of detail, potentially leaving the pharmacist with little direction prior to the patient interview. This concern was highlighted as a potential downfall of the service in a qualitative review that was conducted in 2008 [15]. To address this issue, the enrolling researchers will use a specifically designed database that allows baseline data collection to automatically populate sections of the HMR referral. The referral letter will still be sent to the GP for approval and addition of any further information, such as medications that have changed since discharge. GP approval is a requirement for payment under the existing public service arrangements, and having the GP engaged with the intervention early should increase their willingness to participate. This new approach, however, relieves the GP from having to complete most of the referral data and allows for simple addition of only useful information. The GP may also find the information on this referral letter useful when they receive the letter, as previous research has demonstrated that standard discharge letters following ACS admissions do not always contain a sufficient level of information and sometimes take too long to reach the GP [3].

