### Statistical analysis

All baseline variables will be compared between the control and intervention groups using independent samples t-tests for continuous variables and chi-squared analysis for categorical variables. All outcomes will be reported as descriptive comparisons between the control and intervention groups, with significance reported at alpha = 0.05. Where primary outcomes reach statistical significance, any noted difference in the baseline group comparison will be tested by univariate comparison with stepwise addition into a multivariate model for those with univariate significance of *P *< 0.1. Changes in each group's questionnaire results between baseline and study endpoints, as well as differences between intervention and control group's questionnaire results, will be reported. Further correlational investigations between questionnaire results and adherence will be reported elsewhere. As there are several potential barriers that may prevent a patient randomized to the intervention group from receiving a dHMR according to the protocol, we will use both an intention-to-treat analysis as well as an on-treatment sensitivity analysis.

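### The six-week baseline questionnaire is chased differently in the two arms, so who answers it, and when, can differ by arm

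*Protocol article*

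**What the plan says.** All participants receive the first questionnaire "at six weeks post-discharge - when the participants will be sent their first questionnaire set" (protocol article, Data collection). The stated reason for this timing is "our intention to gauge each patient's status on each of the questionnaires in the time directly before the HMR". The Secondary outcomes section gives the same role to the quality-of-life instruments: "Quality of life will be measured at six weeks post-discharge as a baseline, pre-dHMR measure".

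After mail-out, Data collection sets out a separate procedure for each arm:

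- Intervention: "Patients in the intervention group will be asked to ensure that they complete their questionnaire before their pharmacist visit". At the visit the pharmacist notes, on the patient's word, if it was done. No telephone call is described, and nothing is said about how a form completed after the visit is handled.
- Control: "Patients in the control group will be given a reminder telephone call if their questionnaires have not been returned by three weeks", counted from mail-out.

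The visit itself is placed in the Intervention section: "Patients in the intervention group will receive a dHMR at approximately two months following discharge as well as usual care".

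The Statistical analysis section then reports "Changes in each group's questionnaire results between baseline and study endpoints", together with differences between the arms in questionnaire results.

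**The concern.** A baseline supports a comparison of change only if it is obtained in the same way in both arms. Here the prompt depends on allocation, and it can act in three ways.

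1. **Response.** Slow responders among controls are sought by telephone. In the intervention arm they are reached only by a request tied to the visit. The patients with a baseline value may therefore be differently selected. Intervention patients who never get a visit, a possibility that the Statistical analysis section acknowledges, have neither the visit as a deadline nor a pharmacist to record completion.
2. **Timing.** A control who answers after the call does so at week 9 or later. A valid intervention baseline must be finished before the visit. The Intervention section itself treats months one to three after discharge as the period of highest risk for stopping medication, so the date of measurement may matter.
3. **Late intervention forms.** Whether the form preceded the visit is recorded on the patient's word, but the article attaches no consequence to that record.

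At stake are the comparisons of change in EQ-5D and SAQ (secondary outcomes) and in the psychological scales (process outcomes).

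**Working it through.** **Timeline, in days after discharge**

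Inputs: mail-out at 6 weeks and control call 3 weeks later (Data collection); visit at about two months (Intervention). Two months is read as 8 weeks (56 days) up to the longest calendar reading (62 days), with an average of 60.9 days, or 60.9 / 7 = 8.7 weeks.

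- Mail-out: 6 × 7 = day 42, both arms.
- Control call: (6 + 3) × 7 = day 63.
- Nominal visit: day 56 to day 62.
- Control call minus nominal visit: 63 − 62 = 1 day to 63 − 56 = 7 days.
- Time for an intervention patient to reply before the visit: 56 − 42 = 14 days to 62 − 42 = 20 days. For controls no closing date is stated.

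**The two procedures side by side**

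| | Intervention | Control |
|---|---|---|
| Mail-out | day 42 | day 42 |
| Prompt described | request to finish before the visit | telephone call if not returned |
| When the prompt bites | before about day 56–62 | day 63 |
| Check on completion | pharmacist's note, by patient report | none needed |

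**Is this only an effect of condensing?** For six and twelve months, Data collection again describes a three-week telephone reminder but does not restrict it to one arm. Only the baseline text names the control group. The difference is therefore stated, not inferred from brevity alone.

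**Can the bias be sized?** No. That would need response rates by arm and the course of each scale over weeks 6 to 9 and beyond, and the article gives neither. The sample size does not help. It reproduces (2 × 186 = 372; 372 / 0.8 = 465 enrolled; 465 / 2 ≈ 232 per arm), but it concerns the primary outcome.

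**The case against.** The strongest defence is that the asymmetry has a purpose. A call at week 9 would usually come too late to secure a pre-visit value in the intervention arm, so that arm gets an instruction tied to the visit instead. The article also does not exclude a call to intervention patients. The visit date is only approximate and depends on GP approval, so a visit at week 9 or 10 would leave no gap. All of this is fair, and it limits the point to a small and variable nominal gap. It explains the difference in procedure but does not remove it: an earlier call to everyone would serve the same purpose.

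Four stronger readings are tempting, and the document does not support them.

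- *The bias favours the intervention.* A reader might infer this because late controls have had longer to recover before baseline. No trajectory is given for EQ-5D, SAQ or the belief scales. For adherence behaviour the protocol expects decline after discharge, in which case a later control baseline would be lower and would shrink the controls' apparent decline. The direction is open.
- *A known number of control baselines have no counterpart.* Any count needs an assumed gain from the call. At 10 to 15 percentage points (assumption) of about 232 enrolled controls, it would be 0.10 × 232 ≈ 23 to 0.15 × 232 ≈ 35 forms. Calling these unmatched would further assume that the intervention prompt recovers nobody. The figure does not size a bias.
- *Blinding is broken.* The blinded assessment promised under Outcomes concerns the six- and twelve-month endpoints. A call asking for a mailed self-report form is not endpoint assessment.
- *The main result is at risk.* MPR comes from dispensing records, and readmission and mortality from hospital and death registers. The only route is indirect: if the primary result is significant, noted baseline differences may be tested for entry into a multivariate model. That would not alter the MPR outcome itself.

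It is also true that between-arm differences are planned, and those at six and twelve months can be made without the six-week value. This softens the problem but does not cover the change scores, and change in quality of life is a named secondary outcome.

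**Conclusion.** The point holds in a limited form. As written, the six-week baseline is collected by a different procedure in each arm, with the control call nominally 1 to 7 days after a two-month dHMR. Response and timing can therefore differ by allocation, and comparisons of change from baseline in the questionnaire scales may be biased by an amount and in a direction that the document does not allow one to derive. The baselines are best described as not collected comparably; that they actually differ is not shown.

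This rests on two readings: that the control-only wording is followed literally, and that about two months means 56 to 62 days. The outcomes touched are secondary and process outcomes. The change is worth making because it is cheap and the Trial status section says recruitment has not begun.

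**What to change.** Use one procedure for both arms:

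- Mail the questionnaire at six weeks (day 42), as now.
- Make the same reminder call to every non-responder in either arm about one week later (42 + 7 = day 49). This is 56 − 49 = 7 to 62 − 49 = 13 days before the nominal visit.
- Set the same reply cut-off in both arms, before the visit window opens. A cut-off at day 60 would not do, because a patient visited on day 56 could answer afterwards and still be accepted.
- Record the completion date on every form. Flag intervention forms completed after the dHMR and do not treat them as pre-dHMR baselines. Because visit dates vary, this check is needed as well as the cut-off.
- Report response and completion time by arm.
- Base the questionnaire conclusions on the between-arm comparison at six and twelve months adjusted for the six-week score, with within-group change as description only. The adjustment relies on the common procedure above, since the score is collected after allocation.

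The cost is some extra reminder calls in the intervention arm, a wording change in Data collection and Statistical analysis, and a shorter reply window for controls, who may return somewhat fewer forms.
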